### 2.2. Interventions

A dose of 2 mg/kg/day of commercial sucralose (Golden Hills) will be administered to participants in the sucralose intervention arm for 4 weeks. This dose is equivalent to 40% of the acceptable daily intake (5 mg/kg/day, FDA). Sucralose will be provided to participants in commercial sachets for mixing into their habitual beverages, to be consumed with their three main daily meals. The sucralose dose will be adjusted according to the body weight using an Excel fact sheet based on its concentration in the sachets (2% m/m in glucose). The control group will receive only pure glucose (dextrose), according to the amount of glucose present in the sachets administered in the sucralose arm. The glucose will be weighed and provided to the patients in separate sachets. Adherence will be monitored by personal phone calls and messages via WhatsApp; also, a daily food record format will be given to the participants to provide the number of sachets consumed during the test days. Later, low-NNS intake will remain during the experiment, according to the researcher’s recommendations.

### 2.3. Meal Tolerance Test

A 2 h MTT will be performed before and after each intervention phase to assess glycemic and insulinemic responses, as well as subjective appetite. Prior to the MTT day, it will be requested that subjects not consume alcohol and do not perform intense exercise during 24 h. On test days, after 12 h fasting, subjects will be appointed to the research center at 7:00 a.m., and they will first complete a 100 mm visual analog scale (VAS) self-reported paper questionnaire (time point 0) to measure subjective appetite [18]. Then, an intravenous catheter will be inserted into the antecubital vein of each subject, and a fasting blood sample will be taken (time point 0) for biochemical determinations. After, subjects will be given a standardized breakfast that consists of a nutritional supplement (Simisure; Modern Strategies; Mexico) and a 22 g Kellogg’s Rice Krispies bar (Kellogg’s Company, Battle Creek, MI, USA). The breakfast’s nutritional distribution will be added up to a total of 210 kcal, 7 g from protein, 38.5 g from carbohydrates, and 3 g from lipids. Blood samples will be collected after this breakfast at 15, 30, 60, 90, and 120 min. Glucose and insulin concentrations will be determined in these blood samples, and the VAS questionnaire will be applied 5 min before each sampling. During the test period, subjects will stay at the research center and will be free to read, use electronic devices, watch television, or engage in conversation.

### 2.4. Subjective Appetite

To assess appetite sensation, a validated VAS will be administered before and after each intervention phase. VAS consists of 100-mm-long lines. Each line´s endpoints are labeled with words indicating the most intense positive and negative appetite sensations. Hunger, satiety, fullness, and prospective food consumption will be assessed. Questions will be asked as follows: (1) How hungry do you feel? (2) How satisfied do you feel? (3) How full do you feel? (4) How much food do you think you could eat?

### 2.5. Anthropometric Measurements and Blood Pressure

Body weight and composition will be measured using a body composition analyzer based on bioelectrical impedance (Tanita, TBF-300A, Mexico City, Mexico). Height will be measured using a portable stadiometer (Seca^®^ 214). BMI will be determined using weight and height measurements, and the classification will be made following the World Health Organization (WHO) guidelines: underweight (<18.5 kg/m^2^), normal (18.5–24.9 kg/m^2^), overweight (25–29.9 kg/m^2^), and obesity (30.0 kg/m^2^). A retractable non-stretching tape measure will be used for waist circumference (WC) and hip circumference (HC) measurements. WC will be measured halfway between the bottom rib and iliac crest, while HC will be taken at the widest part of the buttocks. These measurements will determine the waist-hip ratio. Blood pressure will be measured twice using an Omron HEM-7120 professional portable blood pressure monitor. The two measurements of the blood pressure will be taken within one minute, as recommended in the Clinical Practice Guidelines on the Management of Hypertension [19]. The final reading will be based on the average of two readings recorded. Both the anthropometric and blood pressure measurements will be taken before and after each intervention phase.

### 2.6. Biochemical Determinations

Blood samples from the antecubital vein will be collected before and after each intervention phase to determine glucose, insulin, triglycerides, TC, and HDL-C. Serum samples that will not be immediately analyzed will be stored at −70 °C until further analysis. Glucose, cholesterol, HDL-C, and triglyceride determinations will be performed using a Spinreact, Spin200E Clinical Chemistry Autoanalyzer. Insulin will be measured by chemiluminescent microparticle immunoassay assay (CMIA) using a Wiener Lab CLIA-900 System, Rosario, Argentine. To estimate insulin resistance (IR), the homeostatic model assessment index (HOMA-IR) will be used. This is calculated by multiplying fasting glucose (mg/dL) and insulin (μU/mL) concentrations, then dividing by 405 [20].

### 2.7. Gut Microbiota Composition

The fecal samples will be collected for gut microbiota analysis before and after each intervention phase. Microbial DNA extraction from fecal samples will be performed using the QIAamp^®^ Fast DNA Stool Mini Kit (QIAGEN, Hilden, GE, USA) (Cat No. 51604) according to the manufacturer’s instructions. DNA concentrations will be measured with the Nanodrop 2000 (Thermo Fisher Scientific, Waltham, MA, USA). The 16S ribosomal RNA (rRNA) gene will be amplified by polymerase chain reaction (PCR). The PCR products will be visualized using agarose gels.

## 3. Procedure

### 3.1. Ethical Aspects

Research will be conducted in accordance with the principles of the Declaration of Helsinki. The study protocol was approved on 22 April 2021 by the Ethics Committee of the Universidad Juárez Autónoma de Tabasco (UJAT) (No. 0724), and it was registered on 10 April 2021 at the Australian New Zealand Clinical Trials Registry (ACTRN12621001531808). This trial will take place at the División Académica de Ciencias de la Salud (DACS) at UJAT. Informed consent will be obtained from participants by trained research coordinators., who will explain the study’s aims, potential risks, and participants’ right to withdraw from the experiment at any time. Personal information from enrolled participants will be collected and stored confidentially. As part of the informed consent process, participants will be informed that the study protocol includes the collection of blood and fecal samples.

### 3.2. Trial Design

This study is a crossover, randomized controlled trial (RCT) to determine the effect of daily intake of sucralose on glycemic response, subjective appetite, and GM in subjects with overweight or obesity. Participants will be invited to attend the laboratory for preliminary measurements and baseline data after providing written informed consent. Following this, they will be randomly allocated into one of two treatment groups to receive either sucralose or glucose (control) daily for four weeks, each phase separated by a four-week washout period. An MTT, subjective appetite assessment, and stool collection will be carried out before and after each intervention phase (four measurement points). A flow diagram of the study protocol is shown in Figure 1, and the participant timeline actions are presented in Table 1.

### 3.3. Recruitment

Trial participants who are overweight and obese will be screened and recruited by researchers at the DACS of the UJAT from Villahermosa, Tabasco, Mexico. Moreover, information flyers via social media containing the details of the trial will be posted at respective institutions, hospitals, and other public places. The researchers will enroll patients by the inclusion and exclusion criteria. Patient recruitment started in September 2023. A computer-based online random number generator (www.random.org) will be used to allocate participants to the respective interventions, either sucralose or glucose. Randomized treatments will be supplied in sealed envelopes.

### 3.4. Safety Assessment

Each participant will be assessed for any adverse events during the clinical study. Sucralose consumption may cause mild discomfort related to its high sweetness power; however, this will depend on the sensitivity of the participant. At the site of the venous puncture, a bruise and/or a sensation of mild pain may appear. Some unexpected side reactions may appear, which vary in each subject, and these may not necessarily be caused by the treatments. In case of discomfort or adverse effects, participants will be treated by a healthcare provider.

### 3.5. Data Collection and Management

The research staff will interview subjects to gather demographic information and other baseline characteristics of the study group, including NNS consumption frequency, anthropometric measures, and medical history (comorbidities, medications, smoking). All participants will receive medical and nutritional sessions during and following the study. At no time will the participants be identified by the publications or presentations derived from this study, and each of the data provided will be handled with absolute confidentiality. Stool samples will be used exclusively for genetic analysis of the bacteria. The genetic information of the participants will not be studied or analyzed.

### 3.6. Statistical Analysis

Sample size calculation was performed using NCSS and PASS v. 11.0 software. To detect a difference of 10% in the primary outcome variable (glycemic response AUC) and considering a power of 80% and a type 1 error of 5% in a crossover design, a sample size of 19 participants was calculated. However, to allow for a dropout rate of 20%, 24 participants will be considered. Four samples per participant will be analyzed: two baselines and two endpoints. The primary analysis will be performed using GraphPad Prism v. 7.0 and QIIME Software. The D’Agostino and Pearson tests will be used to determine Gaussian distributions. Differences in fasting biochemical markers will be assessed using a one-way analysis of variance (ANOVA) in combination with Tukey’s post hoc test. Time-course data will be analyzed by two-way repeated measures (RM) ANOVA to assess the effects of treatment, time, and the interaction of treatment and time. The intervention´s effect on GM community dissimilarity will be analyzed with permutational multivariate analysis of variance (PERMANOVA) on the Bray–Curtis distance and visualized with Principal Component Analysis (PCoA). ANOVA, or the Kruskal–Wallis test, will be used to compare alpha diversity using the Shannon index. The Firmicutes/Bacteroidetes ratio (F/B ratio) will be calculated from relative abundances. A *p*-value < 0.05 will be considered significant for all analyses.

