In humans, the effects of realistic doses of sucralose on glucose metabolism have been mostly assessed in healthy subjects. Suez et al. showed a clear alteration in glycemic response after two weeks of consuming sucralose (1.8 mg/kg BW/day equivalent to 34% ADI, FDA), which was correlated with GM alterations [5]. Romo-Romo et al. reported an increase in insulin resistance estimated by the HOMA-IR index after only two weeks of sucralose consumption (2.25 mg/kg BW/day equivalent to 45% ADI, FDA) [6]. Recently, Mendez-García et al. (2022) found an altered glycemic response related to changes in GM composition after sucralose intake (0.65 mg/kg BW/day equivalent to 13% ADI, FDA) for 10 weeks [7]. Conversely, other studies in humans do not identify the harmful effects of sucralose on glycemic response or GM [2,8,9]. Thus, it is unclear whether sucralose can induce metabolic alterations modulated by the microbiota modifications.

Particularly, most previous studies examining glycemic response and appetite modifications to sucralose administration have been largely limited to studies in animal models or individuals with normal body weight [10,11,12,13,14,15,16,17]. However, subjects with increased body weight represent an important group due to their increased risk of developing metabolic diseases such as diabetes, hypertension, and heart disease. For this reason, we will conduct a crossover, randomized, and controlled study in subjects with overweight or obesity. The primary outcome of the study will be the glycemic and insulinemic responses, and the secondary outcomes will include pre-post intervention changes in fasting parameters of glucose, insulin, total cholesterol (TC), high-density lipoprotein cholesterol (HDL-C), and triglycerides. Additionally, pre-post changes in anthropometric measures, blood pressure, GM composition, and subjective appetite will be considered. The knowledge gained in this study about the potential metabolic alterations induced by sucralose will be crucial in guiding recommendations for its use, especially given its widespread presence in the food industry.

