## 2. Experimental Design

### 2.1. Participants

A total of 23 adults of both sexes will be recruited. During the screening process, subjects will assist with an interview with a healthcare provider to determine anthropometric indexes, blood pressure, fasting glucose determination, and medical check-ups. Participants will fulfill the following inclusion criteria: both genders, aged 18 to 50, overweight or obese (25–39.9 kg/m^2^), with fasting glucose < 125 mg/dl, and with a maintained stable weight in the previous three months. Patients receiving antibiotics, probiotics, or prebiotics without the ability to give informed consent, pregnant or breastfeeding women, smokers, or alcoholics who have allergies to sucralose or food intolerance, and those with heart, liver, gastrointestinal, or renal disorders will not be included. Patients who have sensitivity or discomfort related to the high sweetness of the test beverage and patients who need to receive treatments with antibiotics, probiotics, or other treatments with drugs that interfere with carbohydrate metabolism or microbiota integrity during the experimental period will be excluded.

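### Glycemic AUC is the powered primary variable, but no listed test is assigned to it, and the time-course ANOVA that covers the meal test leaves two effects open at 0.05

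*Protocol article*

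**What the plan says.** Section 3.6 (Statistical Analysis) opens with the sizing: "To detect a difference of 10% in the primary outcome variable (glycemic response AUC) and considering a power of 80" per cent. The sentence in full gives "a power of 80% and a type 1 error of 5% in a crossover design, a sample size of 19 participants was calculated". This is the article's only mention of AUC. The Introduction words the primary outcome more loosely: "The primary outcome of the study will be the glycemic and insulinemic responses".

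Section 3.6 then assigns tests by outcome:

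- fasting biochemical markers: one-way ANOVA with Tukey's post hoc test;
- meal-test curves: "Time-course data will be analyzed by two-way repeated measures (RM) ANOVA to assess the effects of treatment, time, and the interaction" of the two;
- community dissimilarity: PERMANOVA on Bray–Curtis distance;
- Shannon index: ANOVA or Kruskal–Wallis.

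A threshold of p < 0.05 applies to every analysis. Section 2.3 (Meal Tolerance Test) sets samples at 0, 15, 30, 60, 90 and 120 min. On visits, section 3.6 says: "Four samples per participant will be analyzed: two baselines and two endpoints".

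**The concern.** A power statement describes one test of one contrast. Here it describes AUC, but the only analysis that covers post-meal glucose works on the time course and yields three effects. Two of these involve treatment, and they answer different questions. The main effect compares glucose averaged equally over the sampling times. The interaction asks whether the curves differ in shape.

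Two things are at stake. A reader cannot tell which p-value decides the primary question, so either could be presented as the result and the 5% error rate is no longer held. In addition, neither effect directly estimates the 10% AUC difference for which the trial was sized.

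**Working it through.** **1. The plan's own figure.** Inputs from section 3.6: difference 10%, power 80%, alpha 5% (two-sided assumed), crossover, N = 19. The article prints no SD, so N can only be solved backwards. For a paired t-test with 18 degrees of freedom (noncentral t), 80% power at N = 19 needs a standardised difference of 0.680. The implied SD of the within-person AUC difference is 10% / 0.680 = 14.7% of the mean, or a within-person SD of 14.7 / √2 = 10.4%. A 2×2 crossover t-test also gives 14.7%. N = 19 can be neither confirmed nor refuted: an SD of 12% needs 14 participants, 16% needs 23 and 20% needs 34. The dropout step reproduces: 19 / 0.8 = 23.75, so 24.

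**2. Two routes to a positive result.** With no effect, and if the main effect and the interaction were independent, the chance of at least one p < 0.05 is 1 − 0.95² = 9.75%. Simulation at N = 19 with compound symmetry gives about 9–10%.

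**3. How far the main effect is from AUC.** Trapezoid weights for the stated times, as shares of 120 min, are:

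| min | 0 | 15 | 30 | 60 | 90 | 120 |
|---|---|---|---|---|---|---|
| AUC | 6.25% | 12.5% | 18.75% | 25% | 25% | 12.5% |
| ANOVA main effect | 16.7% | 16.7% | 16.7% | 16.7% | 16.7% | 16.7% |

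The standardised difference for the main effect is 0.680 × r × √(V_AUC / V_mean). Here r is the equal-weight effect divided by the trapezoid-weight effect. With correlation ρ between time points, V_AUC = ρ + (1 − ρ)Σw², V_mean = ρ + (1 − ρ)/6, and Σw² = 0.195.

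Examples at ρ = 0.5, where V_AUC = 0.598, V_mean = 0.583 and the root of their ratio is 1.012:

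- Effect only at 60–120 min: r = 0.500 / 0.625 = 0.80, so 0.680 × 0.80 × 1.012 = 0.550, and power is 62%.
- Equal effect at every time except fasting: r = 0.833 / 0.9375 = 0.889, so 0.680 × 0.889 × 1.012 = 0.612, and power is 71%. It is 74% at ρ = 0.1 and 70% at ρ = 0.9.

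**4. Power at N = 19 when the AUC test has 80%** (simulation, ρ from 0.3 to 0.9; curve and effect shapes assumed):

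| Effect shape | Main effect | Interaction |
|---|---|---|
| Parallel shift | 80–82% | 5% |
| Proportional 10% rise | 78–80% | 7–46% |
| Follows the post-meal rise, zero at fasting | 65–68% | 78–100% |
| 60–120 min only | 62–64% | 95–100% |
| 15–30 min only | 85–87% | 100% |

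**The case against.** The strongest reply is that this is a condensed article. It does not call the repeated measures ANOVA the primary analysis or the only analysis of the meal test, so an AUC comparison may stand in the full protocol or SAP. That is fair for AUC type, model form and the role of baselines. It is less convincing for the primary test itself, because section 3.6 allots tests outcome by outcome, down to a post hoc method and a distance metric, and passes over the variable it has just powered.

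The second reply is that the main effect is a near neighbour of total AUC. This stands: for a parallel or proportional shift its power is within about 2 points of 80%, and for an early effect it is higher. Where the main effect loses power, the interaction usually gains it.

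A reader might infer more than the article supports:

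- **The trial is badly underpowered because baselines are used.** If the contrast were a difference of pre-post changes with all visits equally correlated, the SD would be 14.7 × √2 = 20.8%, power 51%, and 36 completers would be needed. The variance ratio is 2(1 − ρ_within) / (1 − ρ_between). With pre-post correlation 0.8 and between-phase correlation 0.6 it is 1.0 and power stays at 80%; with 0.7 and 0.5 it is 1.2 and power is 73%. The article gives no correlations, attaches pre-post change to the secondary outcomes, and does not say which contrast was sized.
- **A shared drift would almost surely be declared a treatment effect.** A 94% rejection rate requires the four visits to be four levels of treatment and a 10% drift common to both arms. The article states neither. The rate is 37% for a 5% drift, 15% for 3% and 9% for 2%.

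**Conclusion.** The point holds in a limited form. As section 3.6 is written, the powered variable has no test, and two treatment-related effects are available at 0.05 with neither designated. The consequence that depends least on the shape of the effect is a false-positive chance of about 9–10% against the stated 5%, under compound symmetry.

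The cost in power depends on effect shapes and correlations that are assumptions here. For the main effect it ranges from nothing to a fall to roughly 62–74% when the effect is late or absent at fasting. If the interaction decided, power could lie anywhere from 5% to 100%. The comparison takes AUC as total; the article does not say whether total or incremental AUC was sized. The figures do not show that the sample is too small, nor that the 80% is wrong for an AUC test. They show that the 80% is not attached to any test the article lists.

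**What to change.** State one primary analysis in section 3.6: a single two-sided 5% within-participant comparison of sucralose with glucose on end-of-phase glucose AUC from 0 to 120 min, by the trapezoid rule, with the same AUC type (total or incremental) as in the sizing. A crossover linear mixed model with treatment, period and phase-baseline AUC, and participant as a random effect, would serve and would give the baselines a stated role. A crossover t-test on AUC would also match the sizing. Report the difference as a percentage with its 95% CI.

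Make the time-course ANOVA supportive. Restate the power sentence for the chosen contrast with the SD assumed; if that SD is not about 14.7% of mean AUC, 19 does not follow for a paired or crossover t-test. If the full protocol or SAP already names an AUC test, bring that sentence into section 3.6.

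The cost is analysis wording, with no extra patients, visits or samples. Section 3.3 says recruitment began in September 2023, so the change should be made and dated before outcome data are examined.

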## 4. Expected Results

The present study will investigate the effects of realistic doses of sucralose (40% ADI) on metabolic markers, appetite, and GM changes in subjects with overweight or obesity. The problem of obesity has spread globally, not just confined to developed countries. Over the past decades, there have been predictions that if the current trend continues, most of the adult population worldwide will be overweight or obese by 2030 [21]. In this context, non-nutritive sweeteners have been implemented to lower calorie consumption and, consequently, mitigate the risk of increased body weight [22]. However, some studies have demonstrated its participation in the development of metabolic alterations.

Some studies have focused on assessing the effects of sucralose on fasting glucose or glycemic and insulinemic responses in animal models [14,23,24,25,26,27] and in healthy or with T1D/T2D subjects [2,6,7,9,13,15,28,29,30,31]. Other studies show evidence of changes in appetite parameters from a single-dose consuming sucralose [10,12,17,32,33,34]. However, the limited evidence evaluating the effects of sucralose consumption on metabolic markers, appetite, and GM in overweight or obese subjects is inconclusive [35,36,37,38]. This study aims to provide crucial information to this population by evaluating some different factors that have been separately studied under varying conditions, mainly in healthy individuals. This planned study has several strengths. First, notably, this is an RCT that will evaluate metabolic markers and appetite associated with GM composition as an explanatory variable in subjects with overweight or obesity. Second, a crossover trial will be used to minimize inter-individual variability since each participant acts as his own control. One advantage of this design is that fewer participants compared to parallel trials are needed to achieve the same level of significance in terms of type I and II errors. Third, this study involves realistic doses of sucralose. Fourth, this is a long-term study, as the interventions will consist of four weeks, separated by a four-week washout period. Overall, the findings of this study will assist health professionals in making more informed recommendations regarding the consumption of commercial sweeteners and food products containing sucralose. 

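### The one-way ANOVA and Tukey test for the fasting markers names no within-person term and does not deliver the sucralose-minus-glucose contrast in pre-post change

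*Protocol article*

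**What the plan says.** Section 3.6 sets out the data structure: "Four samples per participant will be analyzed: two baselines and two endpoints". Shortly afterwards it assigns the test: "Differences in fasting biochemical markers will be assessed using a one-way analysis of variance (ANOVA) in combination with" Tukey's post hoc test. The sentence after that reads "Time-course data will be analyzed by two-way repeated measures (RM) ANOVA", so repeated measures is specified there and only for that analysis. Later in the same section, "ANOVA, or the Kruskal–Wallis test, will be used to compare alpha diversity using the Shannon index".

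Two other places bear on the choice. The Introduction says "the secondary outcomes will include pre-post intervention changes in fasting parameters of glucose, insulin", and goes on to list total cholesterol, HDL-C and triglycerides. Section 4 gives the reason for the design: "a crossover trial will be used to minimize inter-individual variability since each participant acts as his own control".

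**The concern.** The four samples from one person are correlated. A one-way ANOVA with no participant term puts the stable differences between people into the residual, which is the variance the crossover is meant to remove. The standard error for comparing sucralose with glucose is then too large, and a real effect on fasting glucose, insulin or lipids may be missed.

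A second problem does not depend on the first. The outcome is a change within each phase, so the treatment question is whether the change on sucralose differs from the change on glucose. That contrast involves all four means. Tukey's test compares means two at a time and never forms it.

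Section 4 says the findings should inform recommendations on sucralose. A non-significant result from an insensitive test could be taken as reassurance.

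**Working it through.** **Inputs from Section 3.6.** 19 evaluable participants, 80% power, 5% type I error (taken as two-sided), a 10% difference in glycemic AUC, and four samples per participant.

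**Assumed.** The document gives no SD and no within-person correlation ρ for any fasting marker. I assume equal correlation between all four samples and show a range of ρ. I also assume the ANOVA groups are the four treatment-by-time cells. The section does not name the groups, but a post hoc test implies more than two.

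**The plan's own figures.** The dropout step reproduces: 19 / 0.8 = 23.75, rounded up to 24. The 19 cannot be reproduced without an SD. Solving backwards, a paired t-test with n = 19 and 80% power needs a standardized difference of 0.680, so a 10% difference implies an SD of the paired difference of 10 / 0.680 = 14.7%. That figure belongs to the AUC. Only the value 0.680 is carried over here, as the effect a paired test would detect with 80% power.

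**Standard errors.** Let σ be the total SD of one measurement. For the difference between two cell means:

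- no participant term: σ√(2/n)
- with a participant term: σ√(2(1−ρ)/n)

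The ratio is 1/√(1−ρ).

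**Hand check at ρ = 0.5.** The true difference is 0.680σ√(2 × 0.5) = 0.680σ, and its actual standard error is σ√(2 × 0.5/19) = 0.229σ.

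- As written: the Tukey threshold is 3.72σ/√19 = 0.853σ. Then (0.680 − 0.853)/0.229 = −0.76, or about 22% power.
- With a participant term: the threshold is 3.75σ√0.5/√19 = 0.608σ. Then (0.680 − 0.608)/0.229 = 0.31, or about 62% power.

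**Simulation** (at least 20,000 trials per setting; one endpoint shifted by the effect; ranges show agreement between separate runs):

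| ρ | SE ratio | Overall F, as written | Overall F, participant term | Tukey endpoint vs endpoint, as written | Tukey, participant term | Actual type I error of F, as written |
|---|---|---|---|---|---|---|
| 0 | 1.00 | 86% | 85% | 63–64% | 62–63% | 5% |
| 0.3 | 1.20 | 68% | 85% | 43–44% | 62% | 1.3–1.4% |
| 0.5 | 1.41 | 45–46% | 85% | 25% | 62% | 0.2–0.3% |
| 0.68 | 1.77 | 17% | 85% | 8% | 62% | 0.03% |

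**Splitting the loss at ρ = 0.5.** From 80% (paired test) to 62% is the price of Tukey's control over six pairs. From 62% to 25% is the price of leaving out the participant term.

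**The contrast.** Write S0, S1 for baseline and endpoint on sucralose and G0, G1 for glucose. The six Tukey pairs are S1–S0, G1–G0, S1–G1, S0–G0, S1–G0 and G1–S0. The contrast that matches the outcome is (S1 − S0) − (G1 − G0), which is none of them. S1–G1 does compare the treatments, but it ignores both baselines.

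**The case against.** The document never says that the samples are treated as independent. The trial is sized as a crossover, Section 4 appeals to self-control, and a condensed article may leave a matching option to a fuller plan. This stands in part: the independent-groups reading is an inference. It is a strong one, because the authors write repeated measures where they mean it, and because the non-parametric alternative for alpha diversity, Kruskal–Wallis, is itself an independent-groups test. The missing contrast remains under either reading.

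A reader might infer that most of the power is lost. The document does not support that without a correlation. The loss is nil at ρ = 0 and moderate at 0.3, and it passes half of the power only from roughly 0.5 upward. Part of the gap from 80% also comes from multiplicity control and not from lost pairing.

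The power figures compare endpoints, not changes. For a paired comparison of changes under the same assumptions, the SD is √2 × 14.7 = 20.8, and power for a 10% difference is about 51%. The table therefore measures the cost of omitting the participant term and is not a forecast for the change contrast.

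Finally, the error is conservative and concerns secondary outcomes. Both points stand.

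**Conclusion.** The point holds as a mismatch between a stated test and the stated design. As written, the fasting-marker analysis omits the within-person term. At ρ = 0.5 this inflates the standard error by a factor of 1.41 and cuts Tukey power for the endpoint comparison from about 62% to 25%; at ρ = 0.3 power falls to 43–44%. These sizes rest on an assumed common correlation, four cells and 19 evaluable participants. The absence of the change contrast rests on none of those correlations.

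Three wider readings should be resisted. The sentence does not raise the false-positive rate: when ρ is above zero, the actual type I error falls below 5%. It does not touch the primary glycemic AUC or its sample size. It also does not extend to anthropometry or blood pressure, to which Section 3.6 assigns no named test. The wording should be corrected before analysis, but the trial's main conclusion does not depend on it.

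**What to change.** For the fasting biochemical markers, replace the one-way ANOVA and Tukey test with a within-person analysis that reports a single sucralose-minus-glucose contrast with its 95% CI. One suitable form is a mixed model of the end-of-phase value, with treatment, period and phase baseline as fixed effects and participant as a random effect. The minimum is a paired comparison of the two pre-post changes. That answers the right question, but it does not adjust for period, and under the assumptions above it has about 51% power for the benchmark effect.

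The cost is a change of analysis wording and software that fits the model. No new data, visits or participants are needed.
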